## 5.4 Potential effect modifiers

Stratification into different population groups by age group (18-64, 65-79, 80+ years) and sex will be performed. Given that vaccine effectiveness may differ amongst previously infected individuals, we will stratify analyses by previous confirmed infection status when adequate numbers are available for meaningful statistical analysis. As noted above, we will also stratify analyses by vaccine type.

## 5.5 Analytical techniques

### 5.5.1 Descriptive analysis

We will commence analysis by conducting descriptive analyses to visually inspect trends in vaccination delivery, age-specific COVID-19 hospitalisations and COVID-19 deaths, including by age group and sex. This will include inspecting the number of people who have received no doses, one dose and two doses and the length of time between the receipt of one dose and two doses.

### 5.5.2 Matched analysis

To create control groups for our primary analysis, we will emulate a ‘target trial’. We will do this by conducting 1:1 risk-set matching to identify individuals who had not yet become exposed (i.e. remained unvaccinated) on the date an exposed person received their vaccine dose. We will do this using a time-varying propensity score matching algorithm, by fitting separate propensity score models by month.

Due to the strong confounding effect of living in an elderly care home (arising from the targeted vaccination of these residents and their high risks of COVID-19 harms) and the lack of available controls, we will exclude people whose household had more than 10 people with an average age of 65 years and over. This will be used as a proxy for those living in an elderly care home.

We will incorporate the following characteristics into the time-varying propensity score model: sex, age (grouped in 5 year bands), SES, number of risk factors (grouped), number of previous SARS-CoV-2 tests pre-vaccination era (grouped), geography (local authority level), urban-rural settlement, average household age, number of people in household (grouped), smoker indicator, BMI (grouped), presence in hospital status (hospitalised for any reason 4 weeks prior to monthly time-period) and previous positive test indicator (tested positive previous to monthly time-period). Individuals will then be matched using exact matching based on the propensity score in 1% bands, local authority, and age (exact age in years, truncated up to 100 years). The adequacy of the matching will be assessed by checking for imbalance of the individual covariates and the individual risk groups across exposure groups.

We expect that any effects before 14 days for first dose vaccination will reflect programmatic effects (e.g. being instructed not to attend vaccination if symptomatic and reinforcement of behavioural advice to reduce COVID-19 related risks). Follow up will therefore start from day 14 after the date of first dose vaccination (and day 7 after second dose) for both the exposed and control person. It will end for both the exposed and control person on the first of: experiencing the outcome of interest, death (from any cause) or end of follow up period. Unvaccinated controls who become vaccinated will be eligible to become considered as exposed, after follow up is censored for the exposed-unexposed pair at the date of vaccination of the control. Follow-up of the exposure period will also be censored for both the recipient and the control if the partially vaccinated recipient participant received a second dose. Analyses will be stratified by vaccine type.

For the matched cohort analysis, we will draw Kaplan Meier curves to inspect cumulative incidence. We will then fit Poisson regression models to estimate rate ratios (RRs) with 95% confidence intervals (95% CIs) for the association between exposure group and risk of the outcomes, at weekly time periods from exposure to event (Section 4.2).

We will fit a model including a spline with person-time defined in days, to explore the timing of any waning of vaccine effectiveness. The splines will be fit using thin plate regression splines (the R package ‘mgcv’ default settings) with weekly knots from days 14 to the maximum week. The difference between the smooths in the exposure groups will be calculated using methods by Simpson, [7] to obtain smoothed estimated RRs between the exposure groups at daily follow-up periods.

We will assess vaccine waning using two different pre-specified approaches: first, conducting statistical hypothesis tests for declining effectiveness; and second, by assessing whether effectiveness is maintained above a minimum acceptable level. For the former, we will assess the curvature of the association in the spline modelled estimates over time, to evaluate whether the smoothed estimates peak and return to null. This will be achieved by fitting the same statistical model as for the spline but replacing the spline term with a quadratic term and post 14 days only. A statistically significant positive quadratic coefficient from this model in the exposed group would suggest waning. For the latter approach, we adopted the US Food & Drug Administration’s threshold of achieving a RR of at least 0.5 for the point estimate. [8]

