| Urban/Rural index | 1 Large Urban Areas | 783640 (30.4%) | 784728 (30.5%) | 258154 (31.0%) | 254808 (30.6%) | 525486 (30.2%) | 529920 (30.5%) |
|  | 2 Other Urban Areas | 971117 (37.7%) | 983172 (38.2%) | 318175 (38.2%) | 332206 (39.8%) | 652942 (37.5%) | 650966 (37.4%) |
|  | 3 Accessible Small Towns | 261494 (10.2%) | 259163 (10.1%) | 83271 (10.0%) | 81497 (9.8%) | 178223 (10.2%) | 177666 (10.2%) |
|  | 4 Remote Small Towns | 139935 (5.4%) | 137972 (5.4%) | 44273 (5.3%) | 40936 (4.9%) | 95662 (5.5%) | 97036 (5.6%) |
|  | 5 Accessible Rural | 259551 (10.1%) | 251953 (9.8%) | 76983 (9.2%) | 72623 (8.7%) | 182568 (10.5%) | 179330 (10.3%) |
|  | 6 Remote Rural | 146214 (5.7%) | 144963 (5.6%) | 48979 (5.9%) | 47765 (5.7%) | 97235 (5.6%) | 97198 (5.6%) |
|  | Unknown | 11923 (0.5%) | 11923 (0.5%) | 3884 (0.5%) | 3884 (0.5%) | 8039 (0.5%) | 8039 (0.5%) |
| Number of risk groups ‡ | 0 | 1243982 (48.3%) | 1255925 (48.8%) | 415784 (49.9%) | 432880 (51.9%) | 828198 (47.6%) | 823045 (47.3%) |
|  | 1 | 772262 (30.0%) | 763706 (29.7%) | 245304 (29.4%) | 243424 (29.2%) | 526958 (30.3%) | 520282 (29.9%) |
|  | 2 | 333638 (13.0%) | 330259 (12.8%) | 103715 (12.4%) | 98187 (11.8%) | 229923 (13.2%) | 232072 (13.3%) |
|  | 3 | 132252 (5.1%) | 133286 (5.2%) | 41209 (4.9%) | 37026 (4.4%) | 91043 (5.2%) | 96260 (5.5%) |
|  | 4 | 56040 (2.2%) | 55705 (2.2%) | 17117 (2.1%) | 14192 (1.7%) | 38923 (2.2%) | 41513 (2.4%) |
|  | 5+ | 35700 (1.4%) | 34993 (1.4%) | 10590 (1.3%) | 8010 (1.0%) | 25110 (1.4%) | 26983 (1.6%) |
| Number of previous tests § | 0 | 2105945 (81.8%) | 2100224 (81.6%) | 645635 (77.4%) | 637754 (76.5%) | 1460310 (83.9%) | 1462470 (84.0%) |
|  | 1 | 305290 (11.9%) | 311266 (12.1%) | 110764 (13.3%) | 114364 (13.7%) | 194526 (11.2%) | 196902 (11.3%) |
|  | 2 | 73485 (2.9%) | 73595 (2.9%) | 29242 (3.5%) | 29801 (3.6%) | 44243 (2.5%) | 43794 (2.5%) |
|  | 3 | 24995 (1.0%) | 24719 (1.0%) | 10565 (1.3%) | 10728 (1.3%) | 14430 (0.8%) | 13991 (0.8%) |
|  | 4-9 | 36566 (1.4%) | 36003 (1.4%) | 18077 (2.2%) | 18975 (2.3%) | 18489 (1.1%) | 17028 (1.0%) |
|  | 10+ | 27593 (1.1%) | 28067 (1.1%) | 19436 (2.3%) | 22097 (2.7%) | 8157 (0.5%) | 5970 (0.3%) |
| Smoking status | Ex-smoker | 427097 (16.6%) | 430664 (16.7%) | 135623 (16.3%) | 136623 (16.4%) | 291474 (16.7%) | 294041 (16.9%) |
|  | Non-smoker | 994635 (38.6%) | 1000968 (38.9%) | 327433 (39.3%) | 332476 (39.9%) | 667202 (38.3%) | 668492 (38.4%) |

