### 5.6.3 Covariate balance plot

Standardised mean differences of population characteristics before and after matching for each vaccine

Code: 03c_matching_ps_summary (lines 342-470)

[figure not shown]

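### As written, the propensity score ignores vaccine type although results are reported by vaccine; small, opposite comorbidity imbalances remain within each vaccine, and nothing required removes them from the primary estimates.

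*SAP*

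**What the plan says.** Section 5.5.2 matches each recipient 1:1 to someone still unvaccinated "on the date an exposed person received their vaccine dose". The time-varying score is obtained "by fitting separate propensity score models by month". Comorbidity enters it as "number of risk factors (grouped"), and pairs are then formed by "exact matching based on the propensity score in 1% bands, local authority, and age". Vaccine type appears at none of these steps.

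The same section then states: "Analyses will be stratified by vaccine type". Objective 2 (section 2.2) and sections 5.4 and 5.5.4 also call for results by vaccine.

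On balance, section 5.5.2 promises "checking for imbalance of the individual covariates and the individual risk groups across exposure groups", and section 5.6.3 asks for "Standardised mean differences of population characteristics before and after matching for each vaccine". Neither gives a threshold or an action if balance is poor. The matched Poisson model in section 5.5.2 has no stated covariate adjustment. A doubly robust version is only something the authors will consider (section 5.5.6). Section 5.5.3 commits to an adjusted whole-cohort model, but as a secondary analysis.

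**The concern.** A score for receiving a first dose of either vaccine balances recipients and controls pooled over vaccines. It does not ensure balance among recipients of one vaccine and their own controls if the choice between vaccines depends on covariates. Surplus risk in one vaccine's recipients can cancel against a deficit in the other's, so the pooled table looks clean while each per-vaccine contrast carries residual confounding.

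At stake is the level of each vaccine's rate ratio. Section 5.5.2 judges maintained effectiveness partly by whether the point estimate meets a rate ratio of 0.5, with no allowance for uncertainty, so a shift of a few per cent can matter near that line.

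**Working it through.** **Inputs.** Counts by number of risk groups come from the matched-cohort characteristics table in section 5.6.2. The 5+ row reads "5+ | 35700 (1.4%) | 34993 (1.4%) | 10590 (1.3%) | 8010 (1.0%) | 25110 (1.4%) | 26983 (1.6"%), with columns for both vaccines, BNT162b2 and ChAdOx1, each unvaccinated then vaccinated. Matched totals per arm are 2,573,874, 833,719 and 1,740,155. In every column the six levels sum to the stated total, and the two vaccines add exactly to the combined column at each level.

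**Step 1: reproduce the table.** For 5+ groups, BNT162b2 controls are 10,590/833,719 = 1.3% and recipients 8,010/833,719 = 1.0%. ChAdOx1 controls are 25,110/1,740,155 = 1.4% and recipients 26,983/1,740,155 = 1.6%. These match the printed percentages.

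**Step 2: three or more risk groups.**

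| | Controls | Recipients | Relative difference |
|---|---|---|---|
| Both | 223,992 (8.70%) | 223,984 (8.70%) | 0.0% |
| BNT162b2 | 68,916 (8.27%) | 59,228 (7.10%) | -14.1% |
| ChAdOx1 | 155,076 (8.91%) | 164,756 (9.47%) | +6.2% |

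The recipient/control count ratios at 3, 4 and 5+ groups are 0.90, 0.83 and 0.76 for BNT162b2, and 1.06, 1.07 and 1.07 for ChAdOx1. Chance does not explain this. Treating counts as Poisson, the 5+ difference for BNT162b2 is (10,590 - 8,010)/√(10,590 + 8,010) ≈ 19 standard errors. For ChAdOx1 it is (26,983 - 25,110)/√(26,983 + 25,110) ≈ 8.

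**Step 3: standardised differences.** SMD = (p_v - p_u)/√{[p_u(1 - p_u) + p_v(1 - p_v)]/2}. The largest for any risk-group level is 0.041 (BNT162b2, no risk group). On the mean count, scoring 5+ as 5, the SMD is -0.057 for BNT162b2, +0.017 for ChAdOx1 and -0.006 combined. All are below the customary 0.1.

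**Step 4: effect on the rate ratio.** The factor is Σ p_v,k w_k / Σ p_u,k w_k, where w_k is the relative risk of the outcome with k risk groups. The SAP gives no such gradient, so three are assumed:

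| Assumed w (0 to 5+) | BNT162b2 | ChAdOx1 | Both | Ratio of the two vaccines' factors |
|---|---|---|---|---|
| 1, 1.5, 2, 3, 4, 6 | 0.971 | 1.010 | 0.997 | 0.961 |
| 1, 2, 3.5, 5.5, 8, 12 | 0.953 | 1.016 | 0.996 | 0.938 |
| 1, 3, 6, 10, 15, 25 | 0.937 | 1.021 | 0.995 | 0.917 |

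The ratio of the two rate ratios is therefore shifted by about 4 to 8%.

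**Step 5: set against the 0.5 criterion.** Person-time is nearly equal within matched pairs, so the ratio of day-14+ event counts approximates the rate ratio. BNT162b2: 238/488 = 0.488 (95% CI 0.418 to 0.569). ChAdOx1: 303/541 = 0.560 (0.487 to 0.645). Dividing by the factors in step 4 gives 0.502 to 0.521 for BNT162b2 and 0.555 to 0.548 for ChAdOx1. With the rounded printed rates (2.4/5 = 0.48), BNT162b2 becomes 0.494 at the weakest gradient and 0.513 at the strongest, so the crossing of 0.5 is borderline.

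**Step 6: sampling error.** The crude ratio of rate ratios is 0.488/0.560 = 0.871. The SE of its log is √(1/238 + 1/488 + 1/303 + 1/541), giving a 95% CI of 0.706 to 1.073.

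**Step 7: other covariates.** Ten or more previous tests, the plan's health-worker proxy, has SMD +0.020 for BNT162b2 and -0.020 for ChAdOx1, opposite in sign to comorbidity. Smoking has -0.034 and +0.003, the same sign as comorbidity.

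**The case against.** - **The pooled score is an inference.** The SAP does not say in terms that vaccine type is ignored, and the code was not examined. This stands as a caveat. It remains the plain reading of section 5.5.2, and near-exact balance overall with opposite shifts by vaccine is what a pooled score would produce.
- **The imbalance is small.** This stands: it would pass the usual 0.1 rule. But SMDs give little weight to a shift in a small high-risk tail, which is where this one lies.
- **Safeguards exist.** Section 5.6.3 already plots balance per vaccine and section 5.5.3 plans an adjusted cohort model. Neither corrects the primary matched estimates: the first carries no remedy and the second is secondary.
- **Direction.** A reader might infer that the vaccine comparison is biased in a known direction, favouring BNT162b2. The document does not support that. The direction is shown for comorbidity count only, the previous-tests proxy runs the other way in sign, and net bias over all covariates was not computed.
- **Waning.** A reader might also infer that the waning conclusions are undermined. A constant multiplicative shift moves the level of the log rate-ratio curve, not its curvature, so the quadratic test is largely untouched. The SAP also plans no formal test of one vaccine against the other.
- **Evidence base.** The table uses the Scottish deprivation index inside a template for all nations. Its matched total (2,573,874) differs from the 1,650,185 first-dose matches reported just before it in section 5.6.2. Other nations may show a different pattern.

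**Conclusion.** The point holds in limited form. The level at which the score is fitted, as written, does not match the level at which results are reported. The Scottish table shows the expected consequence: balance overall, with small opposite comorbidity shifts within each vaccine. From comorbidity count alone, the BNT162b2 rate ratio is multiplied by 0.94 to 0.97 and the ChAdOx1 rate ratio by 1.01 to 1.02, so their ratio shifts by 4 to 8%.

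These sizes rest on assumed gradients, on head counts at matching rather than person-time from day 14, and on one nation's data. They lie well inside the sampling error of the crude ratio, although a larger sample would not remove them. The practical exposure is the 0.5 point-estimate criterion. The SAP applies that criterion over time since dose, so the overall rate ratios here only illustrate how sensitive it is. The point is worth correcting, but it is not a gross failure of the matching.

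**What to change.** Preferred: in section 5.5.2, fit the propensity model and match separately by vaccine type within month, comparing recipients of that vaccine with people not yet vaccinated.

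If the existing match is kept, move the covariate-adjusted (doubly robust) Poisson model from the optional list in section 5.5.6 to a required analysis for the per-vaccine rate ratios, including at least number of risk groups, previous tests and smoking.

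In either case, attach to the per-vaccine balance plot in section 5.6.3 a stated threshold and the action to take if it is missed.

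Cost: no new data, but matching or models must be rerun in each nation's research environment. Event counts by arm already stand in section 5.6.2, so the change should be declared as made after they were seen, with results from the existing match reported alongside.

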4.2 Constructed variables

- Time to event in weeks (0-13, 14-20, 21-27, 28-34, 35-41, 42-48, 49-55, 56-62, 63-69 and 70+ days from dose 1, extend to 70-76, 77+ if numbers allow)
- Number of Q Covid risk groups (0,1,2,3,4,5+)
- Number of PCR tests in the pre vaccination era (0,1,2,3-4, 5-9, 10+). This will serve as our proxy for healthcare workers where healthcare worker status is unknown.
- Elderly care home resident (defined as person from a household with more than 10 people and an average age of over 65)

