## 5.3 Potential confounders

Age, sex, socio-economic status (SES), residential settlement measured by the urban/rural 6 fold classification (1 refers to large urban areas and 6 refers to small remote rural areas), household size, number and types of comorbidities commonly associated with COVID-19 illness (asthma, chronic kidney disease, liver cirrhosis, chronic neurological condition, heart failure, diabetes (type 1 and type 2), dementia, coronary heart disease), risk factors (smoking status, blood pressure, body mass index) and geography (local authority level).

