### 5.5.6 Sensitivity analysis

We will consider exploring the impact of alternative approaches to classifying the start of the exposed period (from day 0 of vaccination for both first and second doses, and day 21 after first dose), classifying COVID-19 hospitalisation on the basis of primary diagnosis (rather than any diagnostic position) and using a doubly robust estimator (i.e. including variables for confounder adjustment within regression models that already incorporate a propensity score).

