|  | 4 | 4420 (0.3%) | | 14699 (1.7%) | | 43167 (2.4%) | |  | |  | |
|  | 5+ | 3147 (0.2%) | | 8396 (1.0%) | | 27977 (1.6%) | |  | |  | |
| Number of previous tests § | 0 | 1467860 (83.9%) | | 643067 (74.5%) | | 1477853 (83.6%) | |  | |  | |
|  | 1 | 214044 (12.2%) | | 116474 (13.5%) | | 202719 (11.5%) | |  | |  | |
|  | 2 | 40341 (2.3%) | | 31064 (3.6%) | | 46050 (2.6%) | |  | |  | |
|  | 3 | 9947 (0.6%) | | 11717 (1.4%) | | 15097 (0.9%) | |  | |  | |
|  | 4-9 | 10719 (0.6%) | | 24158 (2.8%) | | 18650 (1.1%) | |  | |  | |
|  | 10+ | 7399 (0.4%) | | 36421 (4.2%) | | 6978 (0.4%) | |  | |  | |
| Average household age ¶ | Mean (SD) | 34.5 (13.9) | | 52 (18.2) | | 54.6 (17.8) | |  | |  | |
|  | Median (IQR) | 31.7 (16.25) | | 54.5 (31.5) | | 55.3 (27.25) | |  | |  | |
| Number of people in household ¶ | 1 | 542866 (31.0%) | | 272231 (31.5%) | | 620387 (35.1%) | |  | |  | |
|  | 2 | 385511 (22.0%) | | 309859 (35.9%) | | 608712 (34.4%) | |  | |  | |
|  | 3-5 | 727433 (41.6%) | | 262802 (30.5%) | | 505624 (28.6%) | |  | |  | |
|  | 6-10 | 81156 (4.6%) | | 16887 (2.0%) | | 30930 (1.8%) | |  | |  | |
|  | 11-30 | 6537 (0.4%) | | 850 (0.1%) | | 1301 (0.1%) | |  | |  | |
|  | 31-100 | 1655 (0.1%) | | 217 (0.0%) | | 222 (0.0%) | |  | |  | |
|  | 101+ | 5152 (0.3%) | | 55 (0.0%) | | 171 (0.0%) | |  | |  | |
| BMI | Underweight | 22839 (1.3%) | | 7172 (0.8%) | | 17856 (1.0%) | |  | |  | |
|  | Normal weight | 221423 (12.7%) | | 108021 (12.5%) | | 216994 (12.3%) | |  | |  | |
|  | Overweight | 1361930 (77.8%) | | 550521 (63.8%) | | 1126894 (63.8%) | |  | |  | |
|  | Obese | 144119 (8.2%) | | 197187 (22.9%) | | 405603 (22.9%) | |  | |  | |
| Smoking status | Ex-Smoker | 135461 (7.7%) | | 140896 (16.3%) | | 299894 (17.0%) | |  | |  | |
|  | Non-Smoker | 659177 (37.7%) | | 343925 (39.9%) | | 679009 (38.4%) | |  | |  | |
|  | Smoker | 283557 (16.2%) | | 200773 (23.3%) | | 436263 (24.7%) | |  | |  | |
|  | Unknown | 672115 (38.4%) | | 177307 (20.5%) | | 352181 (19.9%) | |  | |  | |
| Atrial fibrillation | | | 6268 (0.4%) | | 26750 (3.1%) | | 72957 (4.1%) | |  | |  |
| Asthma | | | 206703 (11.8%) | | 114308 (13.2%) | | 247126 (14.0%) | |  | |  |
| Blood cancer | | | 1811 (0.1%) | | 5358 (0.6%) | | 14739 (0.8%) | |  | |  |
| Heart failure | | | 3408 (0.2%) | | 11265 (1.3%) | | 33232 (1.9%) | |  | |  |
| Cerebral palsy | | | 622 (0.0%) | | 1036 (0.1%) | | 4356 (0.2%) | |  | |  |
| Coronary heart disease | | | 11998 (0.7%) | | 57178 (6.6%) | | 133101 (7.5%) | |  | |  |

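### Comorbidity type is named as a confounder, but only a grouped count enters the primary propensity score, and the balance check on individual conditions has no stated consequence

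*SAP*

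**What the plan says.** SAP 5.3 gives as confounders the "number and types of comorbidities commonly associated with COVID-19 illness" and names the conditions, from asthma to coronary heart disease.

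For the primary analysis, SAP 5.5.2 fits monthly propensity scores containing "sex, age (grouped in 5 year bands), SES, number of risk factors (grouped), number of previous SARS-CoV-2 tests pre-vaccination era (grouped"), then geography, household, smoking, BMI, recent hospital stay and previous positive test. The only comorbidity term is the grouped count. I take it to be the variable defined in 4.2, "Number of Q Covid risk groups (0,1,2,3,4,5"+). Pairs are then formed by "exact matching based on the propensity score in 1% bands, local authority, and age (exact age in years, truncated up to 100 years").

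The Poisson and spline models described later in 5.5.2 compare exposure groups over time since vaccination. No covariates are stated for them.

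Three provisions bear on the gap:

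- 5.5.2 will assess the match by "checking for imbalance of the individual covariates and the individual risk groups across exposure groups". It gives no limit and no action.
- 5.5.6 mentions a doubly robust estimator, "including variables for confounder adjustment within regression models that already incorporate a propensity score", but only as something to be considered.
- 5.5.3 adjusts the whole-cohort models for comorbidities, as a secondary analysis.

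**The concern.** A variable that the plan itself calls a confounder is left out of the design and the model of the primary comparison. Within the count, one condition weighs the same whether it is asthma or heart failure. If the mix of conditions at a given count differs between recipients and controls after matching, the two groups differ in baseline risk and the rate ratio absorbs the difference. The balance check could reveal this, but the plan does not say what would then be done, so the response would be chosen with results in view.

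At stake is a reading against a fixed line. SAP 5.5.2 judges whether protection is maintained by an RR threshold of 0.5 applied to the point estimate, so a bias of a few per cent can change the reading when the estimate is near 0.5.

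**Working it through.** **1. Sections side by side.** Type of comorbidity is in the 5.3 confounder list. It is absent from the 5.5.2 score, from the exact-match keys and from the stated primary outcome models. It is present in the 5.5.2 balance check (no consequence), in 5.5.6 (optional) and in 5.5.3 (secondary, weekly estimates without the spline).

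**2. Does the score balance the count that it does contain?** Inputs are the rows for 3, 4 and 5+ risk groups in the matched-cohort table of 5.6.2.

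| | Controls | Recipients |
|---|---|---|
| BNT162b2 | 41,209 + 17,117 + 10,590 = 68,916 of 833,719 (8.27%) | 37,026 + 14,192 + 8,010 = 59,228 of 833,719 (7.10%) |
| ChAdOx1 | 91,043 + 38,923 + 25,110 = 155,076 of 1,740,155 (8.91%) | 96,260 + 41,513 + 26,983 = 164,756 of 1,740,155 (9.47%) |
| Both | 223,992 of 2,573,874 (8.70%) | 223,984 of 2,573,874 (8.70%) |

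The pooled columns agree almost exactly because the two vaccine strata err in opposite directions. The standardised difference is (p1 − p2)/√{[p1(1 − p1) + p2(1 − p2)]/2}. It is 0.04 for BNT162b2 and 0.02 for ChAdOx1, so these imbalances are small. In the rare top category for BNT162b2 the relative gap is larger: 10,590/8,010 = 1.32, with a standardised difference of only 0.03.

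The table shows no individual condition, so the same check cannot be made for type. The balance plot of 5.6.3 is not reproduced in the text at hand and may cover it. The table's 2,573,874 recipients also differ from the 1,650,185 matched first-dose recipients stated just above it. I therefore use the table as the plan's own illustration and not as a final result.

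**3. Where the estimates lie relative to 0.5.** Events from day 14 come from the same table. The intervals are approximate and treat the counts as independent: ratio × exp(±1.96√(1/a + 1/b)).

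- Both vaccines: 541/1,029 = 0.526 (0.47 to 0.58)
- BNT162b2: 238/488 = 0.488 (0.42 to 0.57)
- ChAdOx1: 303/541 = 0.560 (0.49 to 0.64)

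Moving the first two to 0.5 takes a factor of 0.526/0.5 = 1.05 and 0.5/0.488 = 1.025 respectively.

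**4. Possible size of the bias (assumed inputs).** Let pU and pV be the shares of controls and recipients with conditions whose condition is asthma, and R the outcome rate of other conditions relative to asthma. Then

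bias factor = [pV + (1 − pV)R] / [pU + (1 − pU)R].

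None of pU, pV and R is given for the matched cohort.

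- pU = 0.25, pV = 0.23: from 1.385/1.375 = 1.007 (R = 1.5) to 4.08/4.00 = 1.020 (R = 5)
- pU = 0.30, pV = 0.25: from 1.375/1.350 = 1.019 (R = 1.5) to 4.00/3.80 = 1.053 (R = 5)

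The range is therefore about 1% to 5% among people with conditions. Swapping the groups inverts the factor.

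**5. Dilution to the whole cohort.** With equal counts in both groups, the overall factor is 1 + f(b − 1), where b is the factor from step 4 and f is the share of control events arising in people with conditions. In the matched table 1 − 1,243,982/2,573,874 = 51.7% of controls have a condition. If their event rate is at least that of people without one, f lies between 0.52 and 1. The largest factor above, 1.053, then becomes 1.027 to 1.053 overall.

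**The case against.** **What stands on the other side.** The count is one input to the score and not a match key, and propensity matching aims at balance between groups. A reader might infer bias from the fact that a recipient with heart failure can be paired with a control who has asthma. An unlike pair is not in itself bias, and the document does not show that the groups differ in type after matching. The score also carries partial proxies for severity (recent hospital stay, BMI, smoking, prior testing), the count imbalances are small in standardised terms, and the whole-cohort models do adjust for comorbidities.

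**A tempting larger figure.** In the 5.6.1 table, asthma and severe mental illness make up 356,917 of 537,972 recorded conditions in the unvaccinated (66.3%) against 750,229 of 2,301,698 in the vaccinated (32.6%). A reader might take this as the imbalance at issue. It is not. That unvaccinated column has a mean age of 36 years, whereas matched controls are people not yet vaccinated on the recipient's date, with a mean age of 57.9. The shares also count condition entries rather than people, so they mix type with number.

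**Direction and waning.** A reader might conclude that effectiveness is understated, or that the waning curve is distorted. The document supports neither. The count imbalance itself runs in opposite directions for the two vaccines.

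**What does not answer the point.** The cohort analysis is secondary and fits no spline, so it does not repair the primary waning assessment. The doubly robust model is optional. The balance check has no consequence attached.

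**Conclusion.** The point holds in a limited form: the primary analysis omits a confounder that the plan names, and the one check that would detect the resulting imbalance commits to nothing. The bias from condition type after matching may be negligible; neither its size nor its direction can be determined from the document.

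Under the assumed moderate imbalances it is about 1% to 5% in the RR among people with conditions, and less overall. At the upper end it could change a reading against 0.5. For BNT162b2, 0.488 × 1.053 = 0.513 if controls carry the more serious conditions. For both vaccines, 0.526/1.053 = 0.499 if recipients do, and only without dilution. This rests on the assumed shares and R, and on crude count ratios over the whole of follow-up from day 14 rather than the modelled estimates by time since vaccination.

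The change should be made because it is cheap and removes a conflict between 5.3 and 5.5.2. It is no ground for saying that the estimates are wrong.

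**What to change.** In SAP 5.5.2:

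1. Add indicators for the individual QCovid risk groups to the monthly propensity score models, alongside the count. Include at least the conditions listed in 5.3, and merge rare ones.
2. Check and report balance of the individual risk groups separately for each vaccine, since pooled figures can hide opposite imbalances.
3. State a standardised-difference limit, for example 0.1, and commit to the doubly robust model of 5.5.6 if it is exceeded. The count imbalances shown above (0.04 and 0.02) would not reach 0.1, and rare conditions can differ substantially in relative terms below it, so the sponsor may want a tighter limit for these.
4. Fit the doubly robust model within each nation. The pooling table in 5.6.4 holds only person-days and events by vaccine, period and age group, so condition indicators cannot be used in a model fitted to it.

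**Cost.** Revised wording, a refit of the monthly models, some merging of rare conditions and possibly slightly fewer matches. Table 1 leaves the Northern Ireland cell for clinical diagnoses blank. The count is built from the same risk groups, however, so indicators should exist wherever the count can be formed.
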